## Recruitment and data collection

We will use a mixed-methods (quantitative and qualitative) approach in phase II. The reason for collecting both quantitative and qualitative data is to complement and also to address the shortfalls of either approach. The use of both forms of data allows researchers to gain deeper understanding of the phenomenon under study.^31^ In addition, evidence suggests that triangulation of methods increases both the validity and reliability of data.^32^

The research assistant with the help of health professionals running the NCD clinic at each site will identify the study participants who meet the inclusion criteria consecutively. The research assistants will provide information about the study to the patient and seek written informed consent. Participants will be eligible for the study if they are at least 18 years of age, are attending the NCD clinic for diabetes care and are available for an interview. Participants will be excluded if they require acute medical care or are unable to speak. The research assistants will enrol patients who consent and carry out interviews at the health facility. When patients do not consent to participate in the study, the research assistant will request permission to record sex, age, level of education and occupation of the patient. Adult patients with poorly controlled diabetes (a HbA_1_c level of 8.5% or higher as suggested from previous research^30 33^) and comorbid depression will be recruited for the study and followed up to 6 months after recruitment (figure 3). Data collection will occur at three time points: baseline, at 3 months and at 6 months.

**Figure 3 F3:**
[figure not shown]
Phase II study procedure. EQ-5D, EuroQol Five Dimensions Questionnaire; NCD, non-communicable disease; PHQ-9, Patient Health Questionnaire -9.

Qualitative interviews will be conducted among healthcare workers in order to assess feasibility and acceptability of integrating depression management into NCD care. In-depth interviews will be employed to understand health professionals’ experience in using the validated PHQ-9 for screening and the depression management guidelines.

## Measurements

### The primary exposure variable

Depression will be measured using PHQ-9. PHQ-9 will have been validated in phase I of this study.

The primary exposure of interest is whether the patient is receiving care at an intervention or usual care facility.

### Outcome variables

#### Primary outcome variable

The patient diabetes outcome for this study is blood glucose control. Data on the patients’ status on the primary outcome will be extracted from the NCD patient mastercard. For the purpose of the study in checking how well diabetes is being controlled, HbA_1_c test will be performed on the recruited study participants at baseline, 3 months and 6 months. Depression is the co-primary outcome. PHQ-9 will be administered at baseline, 3 months and 6 months.

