## Sample size determination

The sample size was based on detecting a difference in glycated haemoglobin (HbA_1_c) at 6 months between the study arms. It was based on an analysis of covariance (ANCOVA) approach, with the outcome measurement at follow-up, and the baseline HbA_1_c considered as a covariate in the analysis. The correlation between baseline and follow-up haemoglobin values is estimated to be 0.5. A difference in HbA_1_c between arms of 0.7% is considered to be a clinically important difference (based on a previous study which found a difference of 0.56%,^30^) and data from previous research suggested that the HbA_1_c measurements had an SD of 1.8%.^30^ It is calculated that using a 5% significance level and 80% power; 78 subjects per group are required. It is estimated that there will be a 10% dropout/loss to follow-up. To allow for this, we planned to recruit 87 subjects per group, giving a total sample size for the study of 174 participants.

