### Data analysis

The primary outcome is HbA_1_c at 6 months. This will be compared between groups using ANCOVA. The haemoglobin value at baseline will be considered as a covariate in the analysis.

The HbA_1_c values at 3 months will be considered as a separate outcome, and analysed using equivalent methods to the primary outcome.

Quantitative data will be analysed statistically using SPSS V.20. Descriptive analysis will be done. The recorded qualitative data on the feasibility and acceptability of integrating depression management will be transcribed and coded using Atlas.ti. Relevant queries will be created in the database to thematically analyse the data.

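### Phase II calls depression a co-primary outcome, but its analysis section names HbA1c at 6 months as the primary outcome and its sample size gives the full 5% level and 80% power to HbA1c alone

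*Protocol article*

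**What the plan says.** All of this is in the Phase II part of the protocol article.

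- **Primary outcome variable.** Blood glucose control, measured by HbA1c, is the diabetes outcome. The same paragraph then adds "Depression is the co-primary outcome" and "PHQ-9 will be administered at baseline, 3 months and 6 months".
- **Data analysis.** "The primary outcome is HbA_1_c at 6 months", followed by "This will be compared between groups using ANCOVA", with the baseline value as covariate. HbA1c at 3 months is a separate outcome analysed in the same way. Depression does not appear among the outcomes listed there.
- **Sample size determination.** "The sample size was based on detecting a difference in glycated haemoglobin (HbA_1_c) at 6 months between the study arms". The target is a difference "between arms of 0.7% is considered to be a clinically important difference", with an SD of 1.8% and a baseline to follow-up correlation of 0.5. The result is stated as "using a 5% significance level and 80% power; 78 subjects per group are required". Allowing for 10% dropout, this becomes 87 per group and 174 in total. No effect, SD or power is given for PHQ-9.

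**The concern.** One section gives the trial two primary outcomes, and the other two sections are written for one. This matters because the same result can be read in opposite ways. The intervention trains clinicians to detect and treat depression, so a benefit on PHQ-9 with no difference in HbA1c is a plausible result. Under a co-primary reading where either outcome suffices, that is a positive trial. Under the data analysis section it is not.

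The error rate and power in the sample size section are also tied to the single-primary reading. The whole 5% is spent on HbA1c, so an either-outcome rule has no alpha left for depression. The 80% is the power for HbA1c alone, so under a both-outcomes rule it is not the power of the trial's claim.

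**Working it through.** **1. Reproduce the plan's own figure.** Inputs from the Phase II sample size section: difference 0.7, SD 1.8, correlation 0.5, alpha 5%, power 80%. Sidedness is not stated; two-sided reproduces the figure.

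- Residual variance under ANCOVA: 1.8² × (1 − 0.5²) = 3.24 × 0.75 = 2.43.
- n per group = 2 × 2.43 × (1.960 + 0.842)² / 0.7² = 77.85, rounded up to 78.
- Dropout: 78 / 0.9 = 86.7, rounded up to 87; total 2 × 87 = 174.

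The stated 78, 87 and 174 all reproduce, with 80.1% power at 78 per group. The HbA1c calculation is sound for HbA1c as the only primary outcome. The fault lies in the hierarchy around it.

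**2. If success on either outcome counted, each tested at 5%.** For independent tests, familywise error = 1 − 0.95² = 9.75%. For correlated tests it is 1 − P(|Z1| < 1.96 and |Z2| < 1.96) under a bivariate normal. The article gives no correlation between the two test statistics, so the values below are assumptions.

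| Assumed correlation | Nominal familywise error |
|---|---|
| 0 | 9.75% |
| 0.3 | 9.5% |
| 0.5 | 9.1% |
| 0.8 | 7.8% |

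**3. If both outcomes were required.** Each test can stay at 5% without inflating the error rate. Joint power cannot exceed the smaller of the two powers, so it is at most the 80% for HbA1c. If PHQ-9 also had 80% power (assumed, since no PHQ-9 effect or SD is given):

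| Assumed correlation | Joint power |
|---|---|
| 0 | 0.80 × 0.80 = 64% |
| 0.3 | 66.6% |
| 0.5 | 68.7% |
| 0.8 | 72.9% |

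With higher PHQ-9 power the shortfall shrinks. At independence, 95% power for PHQ-9 gives 0.80 × 0.95 = 76%, and 99% gives 0.80 × 0.99 = 79%.

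**4. If alpha were split at 2.5% each.** The expected test statistic for HbA1c at 78 per group is 0.7 / √(2.43 × 2/78) = 2.80. The two-sided 2.5% critical value is 2.24, so power is Φ(2.80 − 2.24) = 71.3%. Restoring 80% takes 95 evaluable per group. Then 95 / 0.9 = 105.6, so 106 per group and 212 in total.

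**5. If HbA1c were the sole primary, or tested first in a fixed sequence.** HbA1c keeps the full 5%, and 78, 87 and 174 stand.

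**The case against.** The strongest reply is that this is a condensed article. A multiplicity rule, the PHQ-9 model and the PHQ-9 primary time point are commonly left to a full protocol or analysis plan, and neither is shown. That stands: their absence here is not a finding, and nobody can say from this document that the rule will be picked after the data are seen.

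The contradiction can also be read more gently. The outcome section itself distinguishes a primary outcome from a co-primary one, so the analysis section may only be repeating the first label and adding a time point. That softens the conflict but does not remove it. A co-primary outcome shares in the trial's primary claim, and the sample size leaves it neither alpha nor power.

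A reader might infer that the trial will run at nearly double its 5% error rate. The document does not support that. No section says success on either outcome is enough. The inflation disappears if both are required or if HbA1c is the sole primary, and it falls to 7.8% at correlation 0.8. The figures are also nominal: they take each test as holding 5%, whereas the article concedes that baseline differences between its non-randomised clinics may give spurious results.

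Nor can one infer that joint power is 64% to 73%. That range rests on an assumed 80% for PHQ-9. The intervention acts directly on depression, so higher power there cannot be excluded. What is firm is the ceiling of 80%.

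**Conclusion.** The outcome hierarchy is inconsistent as written. Depression is co-primary in the outcome section, while the analysis section names HbA1c at 6 months as the primary outcome and the sample size section assigns the full 5% and 80% to HbA1c. For a two-primary claim the stated error rate and power cannot both be right: an either-outcome rule breaks the first and a both-outcomes rule breaks the second.

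The size depends on which rule applies, and the article does not say. Nominal familywise error is 7.8% to 9.75% over assumed correlations from 0.8 down to 0. Alternatively, joint power is capped at 80%, and is 64% to 73% over the same correlations if PHQ-9 has 80% power. If HbA1c is the only primary outcome, neither problem arises and the sample size is correct.

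**What to change.** Make the three Phase II sections (primary outcome variable, data analysis, sample size determination) agree before analysis.

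**Simplest route.** Keep HbA1c at 6 months as the single primary outcome. Make PHQ-9 at 6 months the first secondary outcome, analysed by ANCOVA with baseline PHQ-9 as covariate, and test it at 5% only if HbA1c is significant. This needs a few sentences in the outcome and analysis sections and leaves 78, 87 and 174 unchanged. The cost is that no confirmatory claim on depression is possible if HbA1c fails, which is a real loss for an intervention aimed at depression.

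**Equally valid route.** Keep two primary outcomes, state whether success needs either or both, and restate alpha or power to match.

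- *Either, at 2.5% each:* HbA1c power with 78 evaluable per group is about 71%, not 80%. Recovering 80% takes 106 recruited per group, 212 in total, which is 38 more than planned.
- *Both, at 5% each:* state the PHQ-9 effect and SD assumed, and report the joint power.

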#### Secondary outcome variable

Quality of life (QoL) will be measured using the interviewer-administered version of the EuroQol Five Dimensions (EQ-5D) Questionnaire. This instrument has been validated in South Africa and Zimbabwe.^34 35^ The tool has been translated into several languages including Afrikaners, Xhosa and Shona.^35^ The EQ-5D Questionnaire will be adapted in Malawi and will be used at baseline and follow-up of patients at 3 months and 6 months.

### Data management

Data will be checked for consistency and completeness by the principal investigator and double entered to SPSS V.20 by experienced data entry clerks. Hard copies of the data will be stored in a locked cabinet and consent forms will be separated from the data.

### Data analysis

The primary outcome is HbA_1_c at 6 months. This will be compared between groups using ANCOVA. The haemoglobin value at baseline will be considered as a covariate in the analysis.

The HbA_1_c values at 3 months will be considered as a separate outcome, and analysed using equivalent methods to the primary outcome.

Quantitative data will be analysed statistically using SPSS V.20. Descriptive analysis will be done. The recorded qualitative data on the feasibility and acceptability of integrating depression management will be transcribed and coded using Atlas.ti. Relevant queries will be created in the database to thematically analyse the data.

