### Phase II: evaluation of the effectiveness of integrating screening using validated PHQ-9 and depression management in physical NCD clinics

#### Study design and setting

In phase II of the study, we will use a quasi-experimental design employing a non-equivalent control group (prepost) design. Prospective controlled interventional trials provide a higher level of evidence for a true causality.^28^ The best choice of the controlled interventional studies is the true experimental design of which RCT is the gold standard. However a non-randomised control group trial is a reasonable choice when an RCT would be ideal but not feasible due to costs and ethics limitations and also when trying to establish the effectiveness of large-scale dissemination and implementation.^28 29^ Furthermore, literature indicates that the interventions often cannot be randomised for the following reasons: ethical considerations, an inability to randomise patients, an inability to randomise locations or settings, and a need to intervene quickly.^29^ We have therefore chosen to use a quasi-experimental design and the intervention programme will be done in two district NCD clinics while the other two districts will provide usual care. Four convenient physical NCD clinics which are implementing the WHO PEN interventions will be allocated to intervention arm (two physical NCD clinics) and control arm (two physical NCD clinics) and in each clinic. Consecutive patients who meet the study criteria will be recruited.

The phase II of the study will be conducted for a period of 9–12 months in four healthcare facilities in Mchinji district, Kasungu district, Salima district and Dedza district of the central region of Malawi (figure 1). The four districts are also implementing the WHO PEN interventions. Currently each district has one physical NCD clinic based at the district hospital. The physical NCD clinics in the four districts are staffed by clinical officers and nurses who have undergone appropriate training in the diagnosis and management of key physical NCDs. They follow similar standard guidelines in the management of physical NCDs.

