### Limitations of the study

In this study, people may have undiagnosed comorbid illnesses and our method of screening may not be strong in capturing other comorbid illnesses. In the first phase of validation we will use two specialised clinics which may not be representative of the wider population. QoL will be measured using five domains and we will therefore not obtain detailed information on the various dimensions that assess health-related QoL. The quasi-experimental design which will be used in the second phase also has a limitation that baseline differences between the clinics may lead to spurious results.

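### Phase II compares non-randomised clinics, but the stated primary analysis adjusts only for baseline HbA1c; about half of any persistent arm difference that baseline HbA1c does not carry would remain as apparent effect.

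*Protocol article*

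**What the plan says.** All references are to the protocol article, phase II.

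- **Study design and setting.** The design is non-randomised: "we will use a quasi-experimental design employing a non-equivalent control group (prepost) design". On the clinics: "Four convenient physical NCD clinics which are implementing the WHO PEN interventions will be allocated to intervention arm (two physical NCD clinics) and control arm", again with two clinics.
- **Data analysis.** "The primary outcome is HbA_1_c at 6 months", and "This will be compared between groups using ANCOVA". One covariate is named: "The haemoglobin value at baseline will be considered as a covariate in the analysis". No other covariate, change-score estimate or sensitivity analysis is named.
- **Sample size determination.** The trial is sized on the same ANCOVA. This section calls the covariate baseline HbA1c, then refers to *haemoglobin* values when giving the correlation of 0.5, so the wording under Data analysis is a slip for HbA1c.
- **Outcome variables.** PHQ-9 and EQ-5D are both measured at baseline, 3 months and 6 months.
- **Limitations of the study**, and the strengths and limitations box after the abstract. Both accept that "baseline differences between the clinics may lead to spurious results". Neither ties an analytic remedy to this.

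**The concern.** In a randomised trial, ANCOVA on the baseline value is the natural choice: the arms differ at baseline only by chance, so the adjustment mainly buys precision. Here the arms are different district clinics, two on each side, and they may differ lastingly in case-mix or care. ANCOVA subtracts only slope × baseline difference. With a slope below 1, part of a lasting difference stays in the treatment contrast and reads as an effect, in whichever direction the clinics happened to differ.

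The protocol names this risk and then fixes a primary model that addresses it through one variable. At stake is whether a difference in 6-month HbA1c can be credited to integrating depression care, a conclusion that the dissemination plan intends for policy briefs.

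**Working it through.** **Inputs from Sample size determination (phase II):** target difference 0.7 percentage points of HbA1c; SD 1.8; baseline–follow-up correlation ρ = 0.5; 5% significance; 80% power; 10% dropout.

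**Assumptions:** two-sided test; equal SDs at baseline and 6 months; ρ is the within-arm correlation; no clustering.

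**1. The plan's own figure.**
- Adjusted SD = 1.8 × √(1 − 0.5²) = 1.559.
- n per group = 2 × [1.559 × (1.960 + 0.842) / 0.7]² = 77.85, so 78.
- 78 / 0.9 = 86.7, so 87 per group and 174 in total.

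The stated sample size reproduces exactly, which confirms the inputs.

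**2. What ANCOVA leaves.** Suppose there is no treatment effect and the arms differ by d at both visits.
- ANCOVA contrast = d − b·d = d(1 − b), with b = ρ × SD(6 months) / SD(baseline).
- At ρ = 0.5 and equal SDs, b = 0.5, so 50% of d remains.
- At ρ = 0.3, 70% remains; at ρ = 0.7, 30%.
- At ρ = 0.5 with an SD ratio (6 months to baseline) of 0.8, 1 − 0.40 = 60% remains; with a ratio of 1.25, 1 − 0.625 = about 38%.

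**3. Illustration, d = 0.5 (assumed).**
- Bias = 0.5 × 0.5 = 0.25, and 0.25 / 0.7 = 36% of the target difference.
- Standard error at 78 per group = 1.559 × √(2/78) = 0.2496.
- False-positive rate = Φ(0.25/0.2496 − 1.96) + Φ(−0.25/0.2496 − 1.96) = 0.169 + 0.0015, about 17%.
- Across ρ = 0.3 to 0.7, the bias from the same gap runs from 0.35 to 0.15.

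**4. Effect of the entry threshold.** Recruitment and data collection (phase II) admits only patients with HbA1c of 8.5% or higher. In a simulation with an underlying gap of 0.7, ρ = 0.5, SD 1.8 and population means of 8 to 10.5 (assumed):
- the ANCOVA contrast stays at about 0.35, the same half;
- a change score leaves about 0.10 to 0.22, against zero without the threshold;
- the gap seen at baseline among recruited patients is only about 0.24 to 0.50.

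So d is the underlying clinic difference. The observed baseline gap would understate it.

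**5. Precision of a change score.**
- SD of change = 1.8 × √(2 × (1 − 0.5)) = 1.8.
- Standard error at 78 per group = 1.8 × √(2/78) = 0.288.
- Power = Φ(0.7/0.288 − 1.96) = Φ(0.47), about 68%.
- For 80% power: 2 × [1.8 × 2.802 / 0.7]² = 103.8, so 104 per group.

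**The case against.** **The bias is conditional.** A reader might infer that the primary estimate is biased as a matter of fact. The documents do not show that. If the arms differ only through baseline HbA1c itself, ANCOVA is unbiased; a change score is unbiased only under parallel trends. Nothing in the article says which case holds or how large a gap to expect. This objection stands, and it makes the 17% an illustration. It does not rescue reliance on one covariate, since convenience allocation gives no ground for assuming the favourable case.

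**The share depends on the correlation.** If 0.5 is the correlation among patients already selected at 8.5% or higher, the 6-month SD would probably exceed the baseline SD, the slope would be above 0.5, and somewhat less than half would remain.

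**The risk is disclosed, and an analysis plan may add more.** Both are fair. There is no concealment, and a fuller document, not shown, could add covariates. But the article names the method and its covariate and sizes the trial on that model, so the point concerns a stated choice.

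**Three further inferences are not supported.**
- *That the pre-post data go unused.* The baseline value is in the model; it is only not used as a change score.
- *That sociodemographic data on phase II participants lie ready.* The phase II recruitment section mentions sex, age, education and occupation only for patients who decline. Collection from participants is plausible but not stated.
- *That the clinics should simply have been allocated by lot.* Study design and setting argues for its choice: "a non-randomised control group trial is a reasonable choice when an RCT would be ideal but not feasible", citing costs and ethics. That design choice is not contested here. A draw of two clinics from four would in any case not secure balance.

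**Conclusion.** The point holds in conditional form. The stated primary analysis of a non-equivalent comparison guards against the conceded clinic differences through baseline HbA1c alone. If a persistent difference exists that this covariate does not carry, about half of it remains as apparent effect at the protocol's correlation of 0.5. Over plausible inputs the share is 30% to 70% for correlations of 0.7 to 0.3, and 38% to 60% for SD ratios of 1.25 to 0.8.

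The result rests on equal SDs, on the correlation being within-arm, and on a persistent gap whose size the documents do not give. Adding the further baseline measures and a second estimate could change what the trial may conclude, so the change should be made. Neither an established bias nor a particular false-positive rate can be claimed.

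**What to change.** 1. Under Data analysis, replace *haemoglobin* with baseline HbA1c.
2. Add baseline PHQ-9 and baseline EQ-5D to the primary model, and age, sex and education if these are recorded for participants.
3. Pre-specify a change-from-baseline (difference-in-differences) estimate as a sensitivity analysis beside the ANCOVA. Compare the direction and size of the two estimates with their confidence intervals; do not require both to be significant. State in advance that, if they diverge materially, the effect will not be attributed to the intervention without qualification.

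**Cost.** The changes are to wording, use measurements already planned, and spend a few degrees of freedom. The second estimate is less precise: about 68% power at 78 per group, and 104 per group (116 after 10% dropout) if it had to carry 80% power, which is why it belongs in a sensitivity role.

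**Limits.** The change score removes a stable difference only under parallel trends, and not fully given entry at HbA1c of 8.5% or higher. Patient-level covariates cannot fully remove clinic-level differences with two clinics per arm. The report should say so.
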